#### 15.2.2 Population for safety analysis

Subjects who are enrolled in this clinical study, underwent living partial liver transplantation, and received NK cells on postoperative day 3 will be the population for safety analysis.

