## 7.5 in-progress total

An interim tally will be made at the end of the observation period of one month after the surgery in the 15th case in which NK cells were administered, and the Effectiveness and Safety Evaluation Committee will consider whether the study should be continued. The Efficacy and Safety Evaluation Committee will determine whether or not to continue the study, based on the achievement of the primary endpoint and from the safety perspective, if the incidence of bacteremia within 1 month after surgery is 6 or more cases (40% or more) out of 15 cases, and if the incidence of adverse events of Stage 3 or higher that cannot be ruled out as causally related to NK cell administration is 2 or more cases. The efficacy and safety evaluation committee will consist of three physicians, excluding the research subcontractor.

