### 12.2 Management of non-conformities in the implementation plan

The principal investigator or sub-investigator may deviate from this protocol if there are unavoidable medical circumstances, such as the need to avoid immediate danger to subjects. In such cases, the principal investigator shall report the details of the deviation or change and the reason for the deviation or change to the Hiroshima University Regenerative Medicine Committee via the head of the research institution as soon as possible. In addition, the principal investigator or sub-investigator shall record all deviations from this protocol, regardless of the reason for the deviation.

If it is appropriate to change or revise the protocol, the draft shall be submitted to the Hiroshima University Regenerative Medicine Committee for approval via the head of the research institution. When changes are made, the ethical, scientific, and medical appropriateness of the changes will be thoroughly reviewed. The procedures for deviations and changes will be in accordance with the established procedures.

(2) When the rehabilitation medical care, etc. is found to be in a state that does not conform to the rehabilitation medical care provision plan, the fact shall be promptly reported to the administrator of the medical institution where the rehabilitation medical care, etc. is provided. In addition, when a particularly serious

non-conformity is found, the opinion of the authorized rehabilitation medical care commission shall be promptly heard.

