### 15.2 Definition of the population for analysis

#### 15.2.1 Efficacy analysis population

Subjects who are enrolled in this clinical study and underwent living partial liver transplantation and NK cells were administered on postoperative day 3 will be the target population for efficacy analysis (the largest analysis set Full Analysis Set: FAS).

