## 15.6 Safety analysis

### *adverse event*

The number of cases, number of incidences, and percentage of incidences of adverse events will be tabulated by event and by severity. The number of cases, number of incidences, and percentage of incidences of adverse events by event type and severity will also be tabulated.

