### 16.4 Effectiveness and Safety Evaluation Committee

#### 16.4.1 Details of deliberations by the Effectiveness and Safety Evaluation Committee

The Efficacy and Safety Evaluation Committee shall consist of three physicians, excluding the subcontractors, and shall deliberate on the following matters

- Contents of the annual implementation status report
- Confirmation of the efficacy and safety of the NK cells and whether the study should be continued at an interim total to be conducted at the end of the observation period of one month after the 15th surgery in which NK cells were administered.
- Assessment of serious adverse events
- Other matters as deemed necessary by the principal investigator or the Efficacy and Safety Evaluation Committee.

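### The safety population in 15.2.2 is tied to infusion on postoperative day 3, so a recipient infused on another day would be exposed but left out of the section 15 safety summaries

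*Protocol*

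**What the plan says.** Section 15.2.2 sets three conditions for the safety population: enrolment, living donor partial liver transplantation, and infusion on the planned day. Subjects who meet the first two and "received NK cells on postoperative day 3 will be the population for safety analysis".

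Section 15.2.1 uses the same three conditions for the FAS: subjects in whom "NK cells were administered on postoperative day 3 will be the target population for efficacy analysis". The two sets therefore have the same content.

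The interim is worded differently. Section 7.5 places it "one month after the surgery in the 15th case in which NK cells were administered", and section 16.4.1 places it "one month after the 15th surgery in which NK cells were administered". Neither states a day. The safety item in 7.5 is a count of recipients: it asks whether the number with "adverse events of Stage 3 or higher that cannot be ruled out as causally related to NK cell administration is 2 or more cases".

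Section 12.2 says that the investigator "may deviate from this protocol if there are unavoidable medical circumstances". Section 15.6 then sets out the adverse event tables: "The number of cases, number of incidences, and percentage of incidences of adverse events will be tabulated by event and by severity". It names no population of its own.

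**The concern.** A safety population should be defined by exposure. The risks that section 10.4.1 lists (infusion reaction, GVHD, infection, contamination of the cells) come from receiving the cells, and a recipient infused a day off schedule carries them too. A condition on adherence to the schedule can be argued for an efficacy set. In a safety set it can only remove people who were treated.

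Two things are at stake. First, nothing in the protocol says where an off-day recipient's adverse events would be tabulated, so on the literal wording they are outside the summaries for that population. Second, the interim committee could count a recipient whom the final safety population does not contain. Collecting safety information is a stated purpose of the study (basis for the design, section 7.1) and adverse events are a secondary endpoint (8.2), so the set that carries this information should not depend on the calendar.

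**Working it through.** **The protocol's own figures.** The denominators below start from the planned size, so that was checked first. The inputs, from section 7.2, are a threshold of 30%, an expected rate of 10%, two-sided 5% significance and 80% power. With the one-sample normal approximation:

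n = [(1.960 × √(0.3 × 0.7) + 0.842 × √(0.1 × 0.9)) / (0.3 − 0.1)]² = 33.1, rounded up to 34.

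This agrees with the stated 34. The target of 37 leaves room for a loss of 3 in 37, about 8% (34/37 = 91.9%). Neither figure depends on the safety population, and neither would change.

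**The wording side by side.**

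| Place | Who is counted | Day condition |
|---|---|---|
| 15.2.1, FAS | enrolled, transplanted, infused | day 3 |
| 15.2.2, safety population | enrolled, transplanted, infused | day 3 |
| 7.5, interim | cases in which cells were administered | none stated |
| 16.4.1, interim | surgeries in which cells were administered | none stated |
| 7.5, safety item | recipients with a Stage 3 or higher event possibly related to the infusion | none stated |

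No section gives a window around day 3 for membership of the safety population.

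**Size of the set.** Let k be the number infused off day. The protocol does not give k, so it is an assumption, shown here from 0 to 3 with all 37 infused. The last column is the exact one-sided 95% upper bound for an event that is never seen, 1 − 0.05^(1/n), where n is the size of the set under 15.2.2.

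| k | Set under 15.2.2 | Exposure-based set | Upper bound under 15.2.2 |
|---|---|---|---|
| 0 | 37 | 37 | 7.8% |
| 1 | 36 | 37 | 8.0% |
| 2 | 35 | 37 | 8.2% |
| 3 | 34 | 37 | 8.4% |

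One off-day recipient is 1/37 = 2.7% of those exposed. The loss of precision is small. What matters is whether an omitted recipient had an event.

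**Interim against final, one assumed case.** Suppose that 1 of the first 15 infused recipients was infused off day and that this recipient had one of two related Stage 3 or higher events. Counting everyone infused gives 2/15 = 13.3%, which reaches the count of two in 7.5. Applying the 15.2.2 condition to the same recipients gives 1/14 = 7.1%, which does not. This shows how the two wordings can part. It is not a forecast.

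**The case against.** The strongest reply is that the case will hardly arise. Perfusate is collected at surgery, the culture lasts three days, the anti-CD3 antibody is added one day before administration (7.4.1), and the product expires on the day of shipment (6.5). A positive infectious disease test, or treatment that is no longer possible, leads to discontinuation of the subject (11.1), and contaminated cells are discarded (10.4.2). These routes produce uninfused recipients, not late infusions. Section 12.2 does not mention moving an infusion, and the Overview does not say that a refusal of permission by the primary physician leads to another day. All of this stands. It limits how often the wording matters and leaves the wording as it is.

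The second reply is that the protocol equates administration with day 3. The headings of 9.2.5 and 9.2.6 do so, and the phrase in 15.2.2 might only describe planned dosing. That is a possible reading, but the phrase stands in the definition as a condition and nothing relaxes it. The reply does weaken the contrast with the interim, because 7.5 and 16.4.1 omit the day without saying that any day counts.

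Three stronger readings are tempting, and the documents do not support them:

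- **That an off-day event would disappear from all reporting.** Case report forms, the annual summary (10.1), expedited reports (10.5.2, 10.5.3), committee assessment of serious events (16.4.1) and the record of every deviation (12.2) do not depend on 15.2.2. The omission is confined to the section 15 summaries for that population. For the adverse event tables it is inferred, because 15.6 names no population and 15.2.2 supplies the only one defined for safety. Section 15.4 names the safety population expressly for baseline data.
- **That the exclusion makes the treatment look safer.** This would need off-day recipients to have a higher event rate than the rest, and nothing in the protocol says so.
- **That the interim and final rules contradict each other outright.** They differ in wording and could give different denominators. No more than that is shown.

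**Conclusion.** The point holds as a defect in the definition. Section 15.2.2 fixes the safety population by adherence to the planned day when it should be fixed by exposure, and no other section says where an exposed recipient infused on another day belongs. Because the protocol settles the set itself, this is not a matter left open for an analysis plan.

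Its size is small and may be nil. If nobody is infused off day, nothing changes. If someone is, each such recipient is 1 of at most 37: 2.7% if all 37 are infused, and slightly more if fewer are (1/34 = 2.9%). The upper bound for an unseen event moves only from 7.8% to 8.4% with three exclusions. The practical consequence is that one severe event in one such recipient could count at the interim and be missing from the final safety summaries. This rests on reading the day phrase as a condition and on at least one off-day infusion taking place. The protocol gives no number for the latter.

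**What to change.** Reword 15.2.2 so that the safety population is every enrolled recipient who underwent living donor partial liver transplantation and in whom any NK cells were administered, whatever the day. List any off-day infusions individually with their day. State in 7.5 that the safety count uses this same set, and align 16.4.1 with it.

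The cost is one sentence in 15.2.2, a clause in each of the two interim sections, and a short listing. No new data are needed, because the follow-up visits in 9.2.6 to 9.2.10 are already timed from the infusion. The sample size of 34, the target of 37 and the FAS are untouched. The change concerns only who is tabulated and takes no view on the infusion day itself.

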### 15.3 Handling of missing values

Withdrawals due to discontinuation or deviations during the course of the study will be reported to the

- ✓ The data observed immediately before the subject's discontinuation or dropout will be analyzed as the last observation data (Last Observation Carried Forward: LOCF).
- ✓ Analysis based on observed values without supplementing missing data (Observed Case: OC)
- ✓ Discontinuation and dropout cases will be analyzed as treatment failure cases (bacteremia cases/ Failure).

The robustness of the results of the analysis by the method of the primary endpoint will be confirmed. The primary endpoint will be analyzed as a failure (failure).

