#### 7.4.6 Duration of study participation of enrolled subjects

The treatment period is from donor graft liver perfusion to the completion of donor liver-derived activated NK cell administration, and the observation period is up to 3 years after living partial liver transplantation surgery.

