## 11 Criteria and procedures for discontinuation of clinical research for each subject

### 11.1 Criteria for discontinuation of clinical research for each subject

The principal investigator or sub-investigator shall discontinue or suspend clinical research on the subject in the following cases

1. If a positive test is found in the infectious disease test of culture test material.
2. In addition to 1) above, if protocol treatment is no longer possible
3. When a subject requests withdrawal of consent for participation in clinical research.
4. When the occurrence of an adverse event is recognized and the principal investigator judges that it is difficult to continue the clinical research on the subject concerned.
5. If it is discovered after enrollment but before the start of protocol treatment that the subject did not meet the eligibility criteria
6. In other cases, when the principal investigator or sub-investigator deems it appropriate to discontinue the clinical research.

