## 15.5 Efficacy analysis

### 15.5.1 Primary endpoints

Incidence of bacteremia within 1 month after living donor liver transplantation  
[Main analysis]

The incidence of bacteremia within 1 month after living donor liver transplantation and its 95% confidence interval will be calculated for FAS. In addition, the following statistical hypothesis test will be performed at a significance level of 5% (two-tailed) by chi-square test using the 30% incidence of bacteremia with non-NK therapy observed in previous studies as a threshold.

The null hypothesis: "The incidence of bacteremia  $p$  in NK therapy is equal to a threshold of 30% ( $p = 0.3$ )."

Counter-hypothesis: "The incidence of bacteremia  $p$  in NK therapy is less than the threshold of 30% ( $p < 0.3$ )"

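### Section 15.3 scores discontinuations and dropouts as bacteremia in the primary analysis without limiting this to recipients whose 1-month status is unobserved

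*Protocol*

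**What the plan says.** Protocol 15.5.1 defines the main analysis: "The incidence of bacteremia within 1 month after living donor liver transplantation and its 95% confidence interval will be calculated for FAS". The incidence is tested by chi-square against 30%, two-sided 5%. The outcome is therefore fixed 1 month after surgery.

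Participation lasts much longer. Section 7.4.6 states that "the observation period is up to 3 years after living partial liver transplantation surgery". The discontinuation grounds in 11.1 carry no time limit. One is "When a subject requests withdrawal of consent for participation in clinical research"; others are an adverse event that makes continuation difficult and the investigator's judgment. Section 11.2 adds that observation continues as far as possible when a subject discontinues after protocol treatment is complete.

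Section 15.3 opens with "Withdrawals due to discontinuation or deviations during the course of the study" and lists three methods: LOCF, OC without imputation, and a failure rule, "Discontinuation and dropout cases will be analyzed as treatment failure cases (bacteremia cases/ Failure"). It then says that robustness will be checked and that the primary endpoint is to be handled by the failure method.

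**The concern.** The failure rule is triggered by a subject's status (discontinued or dropped out), not by the absence of a 1-month outcome. With a 1-month endpoint inside a 3-year study, these are different sets of people. A recipient watched through 1 month without bacteremia who withdraws consent at month 20 is a discontinuation case, yet has no missing primary value. The same holds for a recipient who discontinues in week 2 but is still observed under 11.2.

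If the rule is applied as worded, known non-events become events in the one test that decides the trial. The reported incidence and its confidence interval would then partly reflect long-term attrition. An analyst who follows the wording and one who follows the evident purpose could reach opposite conclusions from the same data.

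**Working it through.** **Inputs.** From 7.2 and 15.5.1: threshold p0 = 0.30, expected rate p1 = 0.10, two-sided 5%, 80% power, 34 required, target 37. From 7.4.6: 3 years of observation, about 35 months beyond the endpoint window. Assumed: q, the share of bacteremia-free recipients who leave after month 1; the protocol gives no figure.

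**The plan's own figure.** n = [1.960 × √(0.30 × 0.70) + 0.842 × √(0.10 × 0.90)]² / (0.30 − 0.10)² = 33.1, rounded up to 34. This reproduces. The step to 37 adds 3 (3/37 = 8.1%), and 7.2 ties it to dropouts at enrollment, so it makes no provision for later leavers scored as events.

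**Critical count.** z = (k/n − 0.30) / √(0.21/n), significant below 30% when z ≤ −1.96. For n = 37, √(0.21/37) = 0.0753.

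| Failures of 37 | z | two-sided p |
|---|---|---|
| 4 | −2.55 | 0.011 |
| 5 | −2.19 | 0.029 |
| 6 | −1.83 | 0.067 |

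At most 5 failures are allowed. With 4 true bacteremias, two bacteremia-free leavers scored as failures lose significance; with 5, one is enough. With 34 recipients the limit is 4: 4/34 gives p = 0.020, and one leaver makes it 5/34, p = 0.052.

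**Power if late leavers are scored as failures.** The scored rate is 0.10 + 0.90q. Power is the exact binomial probability of at most 5 failures in 37, or at most 4 in 34.

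| q (assumed) | scored rate | power, n = 37 | power, n = 34 |
|---|---|---|---|
| 0 | 10.0% | 84.0% | 75.0% |
| 3% | 12.7% | 67.3% | 56.3% |
| 5% | 14.5% | 54.7% | 44.0% |
| 10% | 19.0% | 27.0% | 19.9% |

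At n = 37, q = 3% is about one person (37 × 0.90 × 0.03 = 1.0) and q = 10% about three (3.3).

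**Direction.** At a true rate of 30%, the chance of at most 5 failures in 37 is 1.7%. Adding scored leavers raises the failure rate, so this chance can only fall. The false-positive risk is not inflated.

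**Whom the rule reaches.** The FAS in 15.2.1 contains only recipients given NK cells on postoperative day 3, so those who stop before infusion are outside it. Within the FAS the rule acts only on post-infusion leavers, and nearly all of the follow-up in which they can leave lies after the endpoint window.

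**The case against.** The strongest reply is that the rule sits under the heading "Handling of missing values". A recipient observed to 1 month has no missing primary value, so on this view the rule never touches that recipient. Section 15.5.1 supports this, since it describes incidence within 1 month and no composite with later withdrawal. So does the interim tally in 7.5 and 16.4.1, which counts bacteremia within 1 month after the 15th treated case completes its month and takes no account of later dropout. The opening sentence of 15.3 also breaks off as it stands ("Withdrawals due to discontinuation or deviations during the course of the study will be reported to the"), so its wording about the course of the study cannot settle the scope. Section 11.2 fits equally well with using the outcomes it collects.

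All of this stands as evidence of intent. A reader might infer that the protocol definitely turns every later leaver into a bacteremia case, or that the primary result must stay open until the last 3-year visit. The documents do not support either: no sentence says an observed result is overwritten, and none delays the primary analysis.

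Two further points also stand. Failure imputation is a recognised conservative choice, here paired with LOCF and OC checks. Section 21 describes regular outpatient visits continuing after the study, which makes heavy late loss less likely.

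What does not stand is that the matter can be left alone as detail for an analysis plan. The protocol already states the rule and assigns it to the primary endpoint, and the rule and closing sentence are not limited by time or by missingness.

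**Conclusion.** The point holds as a defect of wording with real consequences. Section 15.3 does not limit failure scoring to FAS recipients whose bacteremia status through 1 month is unobserved, and read literally it would replace observed non-events with events. The heading and 15.5.1 make it likely that this was not meant.

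If the literal reading were applied, one or two leavers could change the conclusion, and power at n = 37 would fall from 84.0% to 67.3%, 54.7% or 27.0% at q of 3%, 5% or 10%. These power figures rest on the literal reading, on a true rate of 10% and on assumed values of q; the changes in p-value need only the counts shown. The bias runs against NK therapy, so the risk is a missed effect and an overstated incidence, not a false claim of efficacy.

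**What to change.** Add to 15.3:

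- The observed bacteremia status through 1 month after surgery is always used for the primary endpoint, including status observed under 11.2 after discontinuation, whatever happens to the subject later.
- Only FAS subjects whose status through 1 month cannot be determined are scored as failures in the primary analysis.
- LOCF and OC are sensitivity analyses for those undetermined cases.

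Complete the broken opening sentence at the same time. The cost is a few sentences in a protocol revision, with no extra data, visits or patients. It should be settled before the primary analysis.

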## 15.4 Subject background and baseline characteristics

For each of the safety and efficacy analysis populations, the subject background and baseline characteristics are summarized using summary statistics and listed in the table. The data used as the baseline is the preoperative data, and if there is more than one data, the most recent data on the date of surgery will be used.

In addition, the number and percentage of subjects who completed this clinical study and the number of subjects who discontinued should be summarized for each discontinuation period, and the reasons for discontinuation should also be summarized.

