#### 7.4.2 Method

- 1) Preparation of Activated Natural Killer (NK) Cells from Liver Transplant Donor Livers  
It is shown in the section "Manufacturing Methods."

- 2) Administration of activated natural killer (NK) cells derived from liver transplant donor livers

After culture and confirmation of safety by infectious disease testing, a single dose of cell suspension is administered intravenously over 30 minutes to 1 hour to liver transplant recipients on day 3 after living partial liver transplantation.

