### 9.2.5 Day of NK cell administration (postoperative day 3)

[Before NK cell administration]

- ① Clinical manifestations: symptoms of infection, presence of treatment for infection, other clinical manifestations
- ② Vital signs: blood pressure, pulse rate, body temperature
- ③ Blood test

<Hematological examination>: Same as preoperative examination

Biochemical tests

Total bilirubin, Direct bilirubin, ALB, AST, ALT, γGTP, ALPH, CRP, BUN, Cre, Na, K, Cl, PT, IgG, IgM, CNI blood levels

- ④ Urinalysis: protein qualitative, sugar qualitative, occult blood qualitative
- ⑤ Immunological analysis

Peripheral blood flow cytometry (phenotyping): T cell %, NKT cell %, NK cell %, CD69 on NK cell, TRAIL on NK cell, NKp44 on NK cell, NKp46 on NK cell, cytotoxicity test

⑥ Diagnostic imaging: simple chest x-ray

[After NK cell administration.]

① Clinical manifestations: symptoms of infection, presence of treatment for infection, other clinical manifestations

② Vital signs: blood pressure, pulse rate, body temperature

③ Blood test

<Hematological examination>: Same as preoperative examination

Biochemical tests

Total bilirubin, Direct bilirubin, ALB, AST, ALT,  $\gamma$ GTP, ALPH, CRP, BUN, Cre, Na, K, Cl, PT

④ Observation of adverse events

Adverse event name, date of occurrence, grade, severity, treatment, outcome/decision date, causal relationship, comments (details of decision to continue, causal relationship, course, etc.)

The name of the adverse event should be recorded by the diagnosis. The name of the adverse event should be recorded with the name of the diagnosis. However, symptoms and signs that cannot be given a diagnosis should be recorded with the name of the symptom or sign.

Check for infections, use of antibiotics, and rejection.

Patient outcomes (presence/absence of graft failure, presence/absence of death, cause of death), secondary transplantation (presence/absence, timing)

⑤ Confirmation of concomitant treatment: treatment for infections (including prophylactic and anticipatory, therapeutic agent, dose, duration)

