### 15.5.2 Secondary endpoints

#### ① Overall survival time

FAS will be observed from the date of surgery to the date of death (regardless of the cause of death) or the date of confirmed survival, and the survival curve for overall survival will be estimated using the Kaplan-Meier method, and the median overall survival and its 95% confidence interval will be calculated. The median overall survival and its 95% confidence interval will be calculated. The survival rates at 6 months, 1 year and 3 years and its 95% confidence interval will be calculated. The Greenwood method will be used to calculate the confidence intervals.

- ② Effect on immune response (evaluation of donor-specific immune responsiveness by CFSE-MLR, detection of DSA, incidence of rejection, evaluation of NK cell activity in recipient peripheral blood).  
For CFSE-MLR and evaluation of recipient peripheral blood NK cell activity for FAS, summary statistics and changes from baseline (mean (median), standard deviation (quartiles)) and their 95% confidence intervals will be calculated for each observation time point. For detection of DSA and incidence of rejection, the number of cases in each category and its percentage will be calculated.
- ③ Hepatocellular carcinoma recurrence / De novo carcinogenesis  
We will observe whether hepatocellular carcinoma (HCC) recurs in FAS and the date of recurrence, and calculate the HCC recurrence rate and its 95% confidence interval, and the mean time to recurrence and its 95% confidence interval. De novo carcinogenesis will be analyzed in the same way.
- ④ Incidence of infectious diseases  
The percentage of subjects who developed bacterial, cytomegalovirus, and fungal infections and their 95% confidence intervals will be calculated. The incidence of infectious diseases by genetic polymorphism will be calculated, and comparisons between genetic polymorphisms will be made using Fisher's direct probability method at a significance level of 5% (two-sided).

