### *vital signs*

Summary statistics of the vital signs are obtained for the change at each time point from the observed values at the scheduled postoperative measurement time points and the observed values at the preoperative examination (baseline) and are listed in the table.

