### *clinical laboratory test results*

Summary statistics of the clinical laboratory data (hematological and biochemical tests) will be obtained and listed for the amount of change at each time point from the observed values at the scheduled postoperative measurement time points and the observed values at the preoperative examination (baseline). For qualitative clinical laboratory data, the frequency of pairs of laboratory category values at baseline and each measurement time point is tabulated in the form of a contingency table.

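### All planned changes in vital signs, laboratory values and NK activity start from the preoperative value and so mix transplant and cell effects; the day-3 pre-infusion assessment is collected but never used as a reference

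*Protocol*

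**What the plan says.** Protocol 15.4 defines one baseline for the whole analysis: "The data used as the baseline is the preoperative data". Where several values exist, the one closest to surgery is taken. Section 15.6 repeats this reference for vital signs ("the observed values at the preoperative examination (baseline) and are listed in the table") and for haematology and biochemistry ("the observed values at the preoperative examination (baseline). For qualitative clinical laboratory data"). For CFSE-MLR and peripheral-blood NK activity, 15.5.2 ② plans "summary statistics and changes from baseline (mean (median), standard deviation (quartiles)) and their 95% confidence intervals will be calculated for each observation time point". No other baseline is defined, so the one in 15.4 applies there too.

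The cells are a single intravenous dose given "to liver transplant recipients on day 3 after living partial liver transplantation" (7.4.2). Section 9.2.5 has a separate block headed "Before NK cell administration". It requires vital signs, haematology, biochemistry, urinalysis, chest X-ray, and flow cytometry with a cytotoxicity test. A second block repeats vital signs and most blood tests after infusion on the same day. Section 9.2 gives the purpose of the study as evaluating the efficacy and safety of administering the cell product to the recipient.

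**The concern.** A change score can show the effect of an intervention only as far as its starting point lies close before that intervention. Here the starting point lies before a different and much larger one. Between the preoperative examination and the infusion, the recipient's whole liver is removed and a graft implanted, blood is lost and transfused (both recorded under 9.2.4), and immunosuppression begins (calcineurin-inhibitor levels are already on the day-3 pre-infusion list). For AST, ALT, bilirubin and PT, the preoperative value describes the cirrhotic liver that was removed and later values describe the graft.

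The trial has one arm and no concurrent control, so no second group is available to subtract the surgical part. The change tables for safety and the confidence intervals for NK activity would therefore answer what happened since before the transplant. The question the study poses concerns what happened since the cells were given. The value needed for that second question is already collected.

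**Working it through.** The protocol gives no figure on this point to reproduce. The check sets the sections side by side, followed by three short calculations.

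**1. What is measured, and how it is used**

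| Time | Measured (9.2, Table 1) | Role in 15.4 to 15.6 |
|---|---|---|
| Preoperative, within 4 weeks before surgery | Vital signs, bloods incl. β-D glucan, urinalysis, flow cytometry, MLR | Baseline |
| Day 3, before infusion | Vital signs, bloods, urinalysis, flow cytometry with cytotoxicity test | Postoperative time point only |
| Day 3, after infusion | Vital signs, bloods (without IgG, IgM, calcineurin-inhibitor level) | Postoperative time point |
| Days 4 and 5 | Vital signs, bloods, urinalysis | Postoperative time points |
| Weeks 1, 2, 4 | As above, plus flow cytometry, MLR and β-D glucan | Postoperative time points |

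The day-3 pre-infusion value is never the starting point of a change.

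**2. What the planned change contains**

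(post − preoperative) = (day-3 pre-infusion − preoperative) + (post − day-3 pre-infusion)

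The first term is complete before any cells are given. To illustrate, assume it is 0.5 to 2 SD and the cells do nothing, with no other change after day 3. The planned change is then 0.5 to 2 SD, and the change from the day-3 value is 0. The shift is an assumption; the protocol gives no figure for it.

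**3. Can the change since infusion be read from the planned tables?**

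Let A = post − preoperative and B = day-3 pre-infusion − preoperative. If the same subjects are present, mean(A) − mean(B) gives the mean change since infusion. Its spread needs the correlation ρ between A and B, which is not among the planned summaries:

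SD(A − B) = √(SD_A² + SD_B² − 2ρ·SD_A·SD_B)

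Take SD_A = SD_B = 1 and n = 34 (the calculated sample size in 7.2). The 95% half-width is 1.96·√(2 − 2ρ)/√34:

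| ρ | SD of A − B | Half-width |
|---|---|---|
| 0 | 1.414 | 0.475 SD |
| 0.5 | 1.000 | 0.336 SD |
| 0.8 | 0.632 | 0.213 SD |
| 0.95 | 0.316 | 0.106 SD |

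The tables thus yield the mean, but leave the half-width anywhere from about 0.11 to 0.48 SD.

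**4. Precision from the two starting points**

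Assume equal variances at all times and n = 37 (the target in 7.2). Let r be the correlation between the starting value and the post-infusion value. Then the SD of change is √(2(1 − r)), and the half-width is t(36)·SD/√37 with t(36) = 2.028. Assumed ranges for r are 0 to 0.4 for the preoperative value and 0.6 to 0.9 for the day-3 value.

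| Case | Preoperative r → half-width | Day-3 r → half-width | Ratio |
|---|---|---|---|
| Closest | 0.4 → 0.37 SD | 0.6 → 0.30 SD | 1.2 |
| Middle | 0.2 → 0.42 SD | 0.8 → 0.21 SD | 2.0 |
| Furthest apart | 0 → 0.47 SD | 0.9 → 0.15 SD | 3.2 |

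A high correlation with the day-3 value is most plausible for the same-day post-infusion sample and much less so for visits up to 3 years later.

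**5. Which items have a day-3 pre-infusion value**

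Vital signs, haematology, most biochemistry, urinalysis and flow cytometry do. CFSE-MLR and β-D glucan do not; both have a preoperative value. Calcineurin-inhibitor levels are on the day-3 list but not the preoperative list, so only the day-3 reference can give a change for them. C7-HRP first appears at week 1 and has neither reference.

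**The case against.** The strongest reply is that the preoperative baseline fits the protocol's own clock. Protocol treatment is counted from graft perfusion (7.4.1), follow-up runs to 3 years after surgery (7.4.6), and the primary endpoint covers the first month after surgery (8.1). Nothing is contradicted, and 15.4 takes the latest preoperative value, so four weeks is an outer limit. This stands, and it is why the preoperative baseline should remain. It does not supply a change since infusion, and the clock is not uniform: both analysis populations require that cells were given (15.2), and adverse events are observed only after infusion (9.2.5).

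A further reply is that the extra table could be left to the analysis plan. The protocol, however, does not leave the reference open; it names one for each of these analyses.

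A reader might infer four stronger things that the documents do not support:

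- *Infusion reactions would be missed.* They are recorded as adverse events with date, grade and causal relationship from just after infusion (9.2.5), graded by CTCAE (10.3) and tabulated (15.6). The paired change would not be the only within-patient evidence.
- *The day-3 data are discarded.* They are a scheduled postoperative time point and would be summarised; what is missing is the paired change.
- *A day-3 reference would isolate the cells.* For NK activity there is no same-day post-infusion sample. The next is at week 1 (9.2.7), and recovery and immunosuppression continue in between.
- *Baseline should simply move to day 3.* A blanket switch would leave β-D glucan without a baseline.

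**Conclusion.** The point holds as a modest and cheap improvement. Sections 15.4, 15.5.2 ② and 15.6 fix a reference under which every change in vital signs, laboratory values and NK activity mixes surgery, immunosuppression and early recovery with any cell effect, and no paired change since infusion is planned. It would go too far to say that these changes measure the transplant instead of the cells; they measure both together.

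The gain is clearest for the same-day change in vital signs and blood tests, where little besides the infusion separates the two values. It is weaker for NK activity, where at least the days up to the week-1 sample intervene. A doubling of precision should not be claimed: the ratio of 1.2 to 3.2 rests on assumed correlations and equal variances. The confidence-interval argument reaches only the immune measures, since 15.6 plans summary statistics without intervals for vital signs and laboratory values.

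The primary endpoint, sample size and interim rule are unaffected.

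**What to change.** - **15.4:** keep the preoperative baseline for the background table. Name the day-3 pre-infusion value as a second reference for items listed in that block of 9.2.5.
- **15.6:** keep the existing change tables. Add the paired change from the day-3 pre-infusion value (mean or median, SD or quartiles) for vital signs, haematology and biochemistry. Include the same-day pre-to-post-infusion change for items on both lists. For qualitative tests, add the corresponding cross-tabulation against the day-3 category.
- **15.5.2 ②:** add the paired change in NK activity from day 3 to weeks 1, 2 and 4, with a 95% confidence interval.
- **Items without a day-3 pre-infusion value:** CFSE-MLR, β-D glucan and others not on that list keep the preoperative baseline. C7-HRP, with neither reference, is summarised as observed.
- **Interpretation:** state that the day-3 reference removes confounding before infusion but not that of later recovery.

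The cost is wording and one extra set of tables. No visit, sample or sample-size change is needed.
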